### Statistical analysis

An intention-to-treat analysis will be used with last available information carried forward to missing data in subsequent measurements. A multilevel linear regression model with repeated measurements will be used (SAS proc Mixed) for continuous outcomes and a hierarchical logistic regression (SAS proc Genmod) for dichotomous outcomes. The effect of self-efficacy, environmental determinants, Portal use, and drop-out during follow-up on primary and secondary outcome measures will be evaluated for their potentially differential effects.

Although the discriminatory power will be limited, an analysis will be carried out as to which subgroups participate in the WHPP and the Health Portal and which subgroups have the best adherence to the lifestyle recommendations (age, sex, education, ethnicity).

In addition, preliminary analyses will be performed for workers with cardiovascular complaints and workers with obesity in order to evaluate whether these subgroups are more or less amendable to changing their lifestyle.

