**Discussion:**

The unique combination of features makes the individually tailored worksite health promotion programme a promising tool for health promotion. It is hypothesized that the Health Portal's features will counteract loss to follow-up, and will increase compliance with the lifestyle recommendations and sustainability of a healthy lifestyle.

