#### Contact with professionals

The fourth feature is the opportunity to seek personal advice from a variety of professionals. By sending a message via the Health Portal participants can consult several experts such as a personal coach, a physiotherapist, or a dietician. This function is added to the Portal to increase adherence to the intervention programme.

The complete Health Portal will be offered for 12 months. After 12 months the monthly contact by a personal coach will be terminated, but access to the Portal will remain throughout the project.

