### Sample size

The assumptions for the power calculations were: an intra-cluster correlation of 0.05 (as observed in a previous cluster RCT in companies [39]), an average of 20 workers per cluster, a power of 80%, and a level of significance of 5% (one-sided). Under these assumptions, we anticipate to be able to detect a difference of at least 12% in prevalence between intervention and control group (e.g. primary outcome measure 30% compliance with the recommendation for PA up to 42%) with 350 workers with completed questionnaires assigned to the intervention. Without a noticeable intra-cluster variance the detectable difference will increase by 9%. With an initial participation of 70% and loss-to-follow-up of 30%, the cluster RCT should invite 2*700 workers.

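### Last observation carried forward, the only stated missing-data rule with 30% loss planned, can bias the 24-month effect in either direction

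*Protocol article*

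**What the plan says.** All references are to the protocol article.

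- **Statistical analysis** fixes the rule: "An intention-to-treat analysis will be used with last available information carried forward to missing data in subsequent measurements". It applies to continuous and dichotomous outcomes alike.
- The same section names the models: "A multilevel linear regression model with repeated measurements will be used (SAS proc Mixed) for continuous outcomes", and a hierarchical logistic regression in proc Genmod for dichotomous outcomes. The primary outcomes, defined in the Abstract as compliance with recommendations, fall under the second.
- It also plans to look at drop-out: "Portal use, and drop-out during follow-up on primary and secondary outcome measures will be evaluated" for differential effects.
- **Sample size** sets the scale of loss: "With an initial participation of 70% and loss-to-follow-up of 30%, the cluster RCT should invite 2*700 workers".
- **Contact with professionals** places a change of intensity between the two follow-up visits: "After 12 months the monthly contact by a personal coach will be terminated". Portal access continues.
- **Objectives** makes a sustained healthy lifestyle part of the aim. The Abstract hypothesises that the Portal's "features will counteract loss to follow-up", and the closing Discussion repeats this as an aim.
- **Study design and population** schedules questionnaires at baseline, 12 and 24 months, but the health check only at baseline and 24 months.
- **Sensitivity analysis** covers subgroups and a bootstrap of the cost-effectiveness ratios. It contains nothing on missing outcomes.

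**The concern.** The rule replaces a missing 12- or 24-month value with the worker's last one and then treats it as observed. Four features of this trial make that risky.

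1. A worker lost before month 12 is given a change of exactly zero, which pulls a true effect towards zero.
2. A worker lost between months 12 and 24 is assigned the state at the end of monthly coaching. Whether behaviour holds once coaching stops is what the sustainability aim asks, and for these workers the rule presupposes that it does.
3. The authors expect the Portal to improve retention. If loss differs by arm and both arms drift over time, more workers in one arm are held at baseline, and retention alone can look like an effect.
4. Cholesterol, blood pressure, body composition and predicted oxygen uptake have no intermediate visit, so everyone without a 24-month check is set to no change. Cholesterol and blood pressure feed SCORE, which in turn enters the cost-effectiveness ratios.

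At stake are the 24-month estimate, the sustainability conclusion and the precision claimed for both.

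**Working it through.** **The plan's own figures.** Inputs from Sample size: ICC 0.05, 20 workers per cluster, 30% against 42%, and "a power of 80%, and a level of significance of 5% (one-sided").

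- Design effect: 1 + (20 − 1) × 0.05 = 1.95.
- Workers per arm, with the control-rate variance in both arms: 180.3 × 1.95 = 351.6, which matches the stated 350. (The usual pooled formula gives 384; this does not affect the present point.)
- Invitations: 350 / (0.7 × 0.7) = 714 against 700 stated. From 700 invited, 700 × 0.7 = 490 enrol and 490 × 0.7 = 343 complete.

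**Expected result under the rule.** Let e be the proportion lost before month 12, l the proportion lost between months 12 and 24, and p0, p12, p24 the true compliance in an arm. Assume drop-outs otherwise resemble completers. The carried-forward prevalence at month 24 is

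(1 − e − l) × p24 + l × p12 + e × p0.

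With equal baselines and equal loss in both arms, and true differences D12 and D24, the bias is

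l × (D12 − D24) − e × D24.

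The second term is dilution from early loss. The first is relapse hidden by late loss.

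**Scenarios.** Control at 30% throughout, total loss 30% in each arm, differences in percentage points:

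| Intervention, month 12 → 24 | True at 24 | All loss early | 15% early, 15% late | All loss late |
|---|---|---|---|---|
| 42% → 42% (sustained) | 12 | 8.4 | 10.2 | 12.0 |
| 42% → 36% (half decay) | 6 | 4.2 | 6.0 | 7.8 |
| 42% → 30% (full decay) | 0 | 0 | 1.8 | 3.6 |
| 36% → 42% (delayed) | 12 | 8.4 | 9.3 | 10.2 |

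For example, sustained with all loss early: 0.70 × 0.42 + 0.30 × 0.30 = 0.384 against 0.30. Full decay with all loss late: 0.70 × 0.30 + 0.30 × 0.42 = 0.336 against 0.30.

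Under full decay, with 490 / 1.95 effective workers per arm and a one-sided 5% test, the chance of declaring a difference at month 24 rises from 5% to about 11% (1.8 points) or 22% (3.6 points).

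**Loss that differs by arm.** Illustrative assumption: no effect, and both arms rise from 30% to 40%.

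- Early loss 20% (Portal) and 40% (control): 0.80 × 0.40 + 0.20 × 0.30 = 38%, against 0.60 × 0.40 + 0.40 × 0.30 = 36%. Spurious difference: 2 points.
- Early loss 25% and 35%: 37.5% against 36.5%. Spurious difference: 1 point.

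**Standard errors.** The ratio of the nominal standard error with filled-in values to that from observed 24-month values, at ICC 0.05 and a fixed set of worksites, is:

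- 20 enrolled and 14 observed per worksite: √[(1.95/20) / (1.65/14)] = 0.91.
- 20 observed and about 28 enrolled: √[(2.35/28) / (1.95/20)] = 0.93.

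Holding the design effect at 1.95 regardless gives √(343/490) = 0.84. That is an upper bound on the shrinkage, because filling in values enlarges clusters without adding worksites.

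**The case against.** The best defence is that the harm is not certain. The article gives a total loss of 30% but neither its timing nor its split by arm. A sustained effect with all loss after month 12 is reproduced exactly, as is half decay with an even split. With a sustained effect the error never favours the intervention when loss is equal. With equal loss and no effect at either visit, no spurious difference arises. The common rise of 10 points and the unequal loss rates are not in the document. All of this stands and limits the claim to what the rule can do.

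It is also fair that missing-at-random is an assumption. If workers leave because they did not change, a model fitted to observed data may overstate benefit, and the baseline value could be closer to the truth. That supports a sensitivity analysis, but it does not make carrying forward a sound main rule.

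Two stronger readings are tempting. A reader might infer that the mixed model already named makes the fill-in unnecessary throughout. It is named for continuous outcomes only; the dichotomous primary outcomes go to proc Genmod and need a different remedy. A reader might also infer that drop-out will be examined on filled-in values, where early leavers show no change by construction. The text does not say which values that examination uses.

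**Conclusion.** The concern holds as a risk of bias in either direction. The rule is written into the main analysis, so it is not a detail left to an analysis plan or lost in condensing an article, and no alternative is stated. In the equal-loss scenarios the error runs from −3.6 to +3.6 points against a design difference of 12. Retention that differs by arm could add 1 to 2 spurious points under the illustrative trend. Nominal standard errors shrink by roughly 7–9%, and by 16% at most.

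A reader might conclude that the 24-month result will be biased, or biased in favour of the Portal. The document does not support that: direction and size depend on when and in which arm workers leave and on how behaviour moves, none of which is given. Nor can the rule be defended as conservative, since late loss followed by relapse inflates the effect. The figures assume that drop-outs resemble completers, a constant 30% in control except where a trend is stated, and the protocol's 30% loss.

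**What to change.** - Remove carrying forward from the main intention-to-treat analysis and keep it at most as a sensitivity analysis.
- Continuous outcomes: fit the repeated-measures mixed model already named to all observed data.
- Dichotomous outcomes, including the primary ones: use a likelihood-based mixed logistic model on observed data, or multilevel multiple imputation that respects worksite, followed by GEE.
- State that these analyses rely on missing-at-random, and report loss by arm and by visit.
- Add a missing-not-at-random check that varies the assumption about drop-outs by arm, such as a delta-adjusted analysis. Counting all drop-outs as non-compliant should not be the only check. In the null scenario with 40% compliance and loss of 20% against 40%, it gives 0.80 × 0.40 = 32% against 0.60 × 0.40 = 24%, a spurious 8 points.
- Keep the planned examination of drop-out, provided it does not use carried-forward values.

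The cost is revised analysis text and modest programming, somewhat more for the dichotomous outcomes because a new model or imputation step is needed. No further data or participants are required. The remaining downside is the dependence on missing-at-random, which the sensitivity check is there to test.

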## Discussion

In this study protocol the design of a pragmatic cluster randomised controlled trial on worksite health promotion is presented. The study is designed to evaluate the (cost)effectiveness of an individually tailored long-term worksite health promotion programme on PA and nutrition. It is hypothesized that the unique combination of critical features (a computer-tailored advice, a monitor function, a personal coach, and the opportunity to contact professionals at request) counteracts the main factors for ineffective WHPP (lack of participation, adherence to the WHPP and sustainability), and leads to a change in lifestyle. By conducting an extensive process evaluation we gain insight into the effective elements of worksite health promotion. By registering several process variables it is possible to find out if participants with a higher adherence to the (separate parts of the) WHPP are more likely to comply with the lifestyle recommendations.

With the health check as starting point for the WHPP, it is aimed to increase participation. The Health Portal's critical features are aimed to counteract loss to follow-up, and increase adherence to the intervention programme, compliance with lifestyle recommendations, and sustainability of a healthy lifestyle. Because of the long-term follow-up, sustainability of healthy behaviour will be facilitated.

The cost-effectiveness of the extensive Health Portal will be compared to the cost-effectiveness of the standard WHPP.

In conclusion, this study evaluates a promising intervention on healthy behaviour and results will provide insight into cost-effectiveness and the effective elements of WHPP.
